### Data management

All the involved participants were coded with a number. We used a case report form (CRF) to record the information of participants, including basic information, shoulder function scores, MRI results, and follow-up. The follow-up duration of each participant will be at least 1 year. We also assessed the shoulder function at four other points, two days after PRP injection, 1 month, 3 months, and 6 months. When participants come back to our hospital for a check, the data will be collected by a blinded physiotherapist, other researchers will be forbidden from obtaining the research data. Besides, statisticians will be blinded in our study.

### Sample size calculation

We used the Constant-Murley score serving as a basis of estimating sample size. Based on the study of Sham et al. [12] and our pilot observations, we consider that the change of Constant score could be 8 with a standard deviation of 20. We calculate that 131 participates for each group will be required with alpha set at 0.05 and a power of 0.8. Considering the 20% drop rate, we will recruit 314 participates in total.

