### Statistical analysis

All statistical analyses will be performed using SPSS 25.0 (IBM Corporation, Armonk, NY). Continuous variables are described as means and standard deviation. We will use independent *t* tests or Mann-Whitney *U* tests to compare 2 groups. If needed, the stratified analysis will be conducted based on the age of participants and the PRP injection site. A *P* value < .05 will be defined as statistically significant.

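### The stated inputs need about 100 per group for 80% power, not 131; 131 per group gives about 90% power

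*Protocol article*

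**What the plan says.** The Sample size calculation section of the protocol article names the endpoint used for sizing: "We used the Constant-Murley score serving as a basis of estimating sample size". Citing a published study and pilot observations, it assumes that "the change of Constant score could be 8 with a standard deviation of 20". It then gives the result: "We calculate that 131 participates for each group will be required with alpha set at 0.05 and a power of 0.8". Dropout is added as a separate, later step: "Considering the 20% drop rate, we will recruit 314 participates in total".

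The Statistical analysis section plans independent t tests or Mann-Whitney U tests between the two groups, and a P "value < .05 will be defined as statistically significant". Neither section says whether the test is one- or two-sided, and neither describes an adjustment that would raise the number. The total of 314 is repeated in the Abstract, in Study design and in the Discussion.

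**The concern.** The section prints every main input to a two-group comparison of means (difference, SD, alpha and power) together with the resulting number per group. The result should therefore follow from the inputs, and it does not. A standardised difference of 8/20 = 0.40 at 80% power is well known to need about 100 per group.

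At stake is the accuracy of one of the few fixed quantitative commitments in the article. On the published figures, a reader would take the chance of missing a true 8-point difference to be 20%; on the same inputs with 131 per group it is about 10%. If the number rather than the power is the wrong entry, the total of 314 is also larger than its stated basis supports.

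**Working it through.** **Inputs**

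| Input | Value | Source |
|---|---|---|
| Difference | 8 points | Sample size calculation |
| SD | 20 | Sample size calculation |
| Alpha | 0.05 | Sample size calculation |
| Power | 0.80 | Sample size calculation |
| Allocation | 1:1 | implied by "131 participates for each group will be required" |
| Sidedness | two-sided | assumption; not stated |
| Meaning of the 8 | between-group difference | assumption; the wording is ambiguous |

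**Attempt to reproduce 131 per group**

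Normal approximation: n per group = 2 × [(z for alpha + z for power) × SD / difference]²

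- 80% power: 2 × [(1.960 + 0.8416) × 20/8]² = 2 × 7.004² = 98.1, rounded up to 99.
- The t test (noncentral t) gives 99.1, rounded up to 100.

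The stated 131 is not reproduced. It is 131/100 = 1.31 times the t-test requirement.

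**Power that 131 per group gives**

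- Normal: 0.40 × √(131/2) = 3.237; 3.237 − 1.960 = 1.277; power = 89.9%.
- t test: 89.7%.

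**What would give 131**

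- 90% power: 2 × [(1.960 + 1.2816) × 20/8]² = 131.3 (normal); 132.3 (t test). Rounded up, these are 132 and 133.
- At 80% power by the t test, 131 needs an SD of 23.0 with the difference at 8, or a difference of 6.95 with the SD at 20. The article states neither.

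**Other readings, all at 80% power**

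| Reading | n per group |
|---|---|
| One-sided alpha 0.05 | 78 |
| Alpha 0.025 (split over two primary outcomes) | 119 (normal), 121 (t test) |
| Mann-Whitney, efficiency 0.955 | 104 |
| Mann-Whitney, worst-case efficiency 0.864 | 115 |
| Alpha 0.025 with Mann-Whitney 0.955 / 0.864 | 126 / 139 |
| Within-group (paired) change | 52 |

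None gives 131. Two near matches conflict with the text:

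- 100/0.8/0.955 = 130.9. This already contains the 20% dropout, which the article applies after 131.
- A 3:1 split needs 66 + 198 = 264 in total, close to 2 × 131 = 262. But the article gives 131 for each group and states no ratio.

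**Effect on the total**

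- The article's 314 comes from 131 × 2 × 1.2 = 314.4.
- With 100 per group and the same multiplier: 100 × 2 × 1.2 = 240, which is 74 fewer.
- With division by 0.8 instead: 100 / 0.8 × 2 = 250. Whether dropout should be handled by multiplying or dividing is a separate matter.

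**The case against.** The arithmetic is hard to dispute, so the case on the other side concerns consequence and remedy.

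- **The error is safe.** The trial is larger than its stated power requires. If 20% of 314 are lost, about 251 remain (125 per group if equal), and power is still about 88%. This stands: no endpoint, test or recruitment target has to change, and a null result should in any case be read from its confidence interval. The harm is to the accuracy of the justification.
- **Power of 0.90 is a conjecture.** The article never mentions 0.90, and the match is not exact, since rounding up gives 132 or 133. The slip could lie in the SD, the difference, the power or the number, and the cited study and pilot data are not shown. This stands as a caution: the sponsor should go back to the calculation actually run. It does not remove the contradiction, because 131 per group gives about 90% power on the stated inputs wherever the slip arose.
- **Equal groups are not assured.** Patients choose their own group. With 251 evaluable, power is about 88% at 50:50, 87% at 60:40, 82% at 70:30 and 78% at 75:25 (the splits are assumptions). This is a fair limit on what any power statement promises, but it cannot explain a figure given per group and before dropout.
- **The total may be unaffected.** If the power is the wrong entry, 314 is untouched by this error. That is correct; the total is in question only if the number per group, or another input, is wrong.

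**Conclusion.** The concern holds. The stated difference, SD, alpha and power require 99 to 100 per group, not 131, and 131 per group gives about 90% power (89.7% by t test), not 80%. The likeliest explanation is that the power was misreported, but the document cannot settle this.

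The conclusion assumes a two-sided test, equal groups, and 8 points as the between-group difference. It does not depend on these choices: a one-sided test (78) or a within-group reading (about 52) moves the requirement further from 131. The discrepancy does not leave the trial short of patients on its own assumptions, so it is a certain error in the published justification with little consequence for the adequacy of the sample.

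**What to change.** Retrieve the calculation that was actually run and make the sentence agree with it. On the stated difference and SD there are two consistent forms:

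1. Difference 8, SD 20, two-sided alpha 0.05, power 0.90, with 131 to 133 per group.
2. The same inputs with power 0.80 and about 100 per group, adding that 131 was kept as a margin.

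If a different SD or difference was used (for example an SD near 23 or a difference near 6.95 at 80% power), report that value instead. In each case state the sidedness, whether the 8 points is a between-group difference, and the visit to which it applies.

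The cost is one corrected sentence. No extra patients are needed, and recruitment can stay as planned.

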**Methods:**

This is a single-center prospective non-randomized study implemented in July 2019 at the Affiliated Hospital of Southwest Medical University in Sichuan. Three hundred-forteen patients with rotator cuff injury aged over 18 years were recruited. Participants were assigned to the experiment group (PRP plus physiotherapy) or control group (PRP) by their desire. We used the Constant-Murley score to assess the shoulder function, the Visual Analogue Scale to evaluate shoulder pain, and the MOS Item Short-form Health Survey (SF-12) to measure the quality of life. MRI was applied to measure tear size, and the follow-up duration is 12 months.

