### Study setting and participants

This study is being performed in the Affiliated Hospital of Southwest Medical University in China, and all participants are recruited from inpatient and outpatient. All patients were screened rigorously according to inclusion and exclusion criteria. Physicians decide whether the patient is enrolled, and they will tell eligible participants the research protocol in detail. Every eligible participant will be asked to sign a written consent before taking part in this study. The participants voluntarily choose to receive rehabilitation programs after PRP injection, then PRP in addition to physiotherapy group and PRP group were formed. The trial protocol is shown in Fig. 1.

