Some limitations should be listed. First, the current study design is a non-randomized study. The evidence level is relatively low. Considering the feasibility and the actual situation, we select non-randomized study with a large sample size to clarify the correlation between PRP and physiotherapy. In our study, the participants have the right to receive physiotherapy or not. Second, it is impossible to blind therapists. We need therapists to protect participants. Except for limitations, we also have some strengths. This is the first study to analyze the PRP injection combined with physiotherapy for patients with rotator cuff injury. The study design is relatively humanized, and the results are objective. In addition, statistics experts will participate in this study to make the results more reliable. Finally, we can easily establish a clinical database based on this study.

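### The 20% dropout allowance is multiplied on rather than divided out, so 314 recruits do not deliver the 131 per group called required; the stated 80% power survives because 131 is really a 90%-power figure

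*Protocol article*

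**What the plan says.** The Sample size calculation section of the protocol article bases the number on the Constant-Murley score and assumes that "the change of Constant score could be 8 with a standard deviation of 20". With "alpha set at 0.05 and a power of 0.8" it concludes that "131 participates for each group will be required". It then adds the allowance for loss: "Considering the 20% drop rate, we will recruit 314 participates in total". The total of 314 is repeated in the abstract, under Study design and in the Discussion. Whether alpha is one- or two-sided is not stated.

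The groups are formed by the patients themselves. The abstract says "Participants were assigned to the experiment group (PRP plus physiotherapy) or control group (PRP) by their desire". Study setting and participants says "The participants voluntarily choose to receive rehabilitation programs after PRP injection", and the limitations paragraph of the Discussion says "In our study, the participants have the right to receive physiotherapy or not". The article gives no allocation ratio, no expected split and no minimum per arm. The planned analysis uses t tests or Mann-Whitney U "tests to compare 2 groups".

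**The concern.** The section prints a per-group requirement, a dropout rate and a recruitment total, and the three do not agree. A 20% dropout rate means that one in five of those recruited is lost, so the requirement has to be divided by 0.80. Adding 20% to it gives a smaller total, and the article's own dropout rate then leaves fewer evaluable patients than the number it calls required.

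The per-group figure also presumes equal arms, while the size of each arm is left to patient preference. If the arms came out uneven, the smaller one would fall further below 131. At stake are whether the article describes correctly what 314 recruits will yield, and whether the trial keeps the power it claims.

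**Working it through.** **Inputs.** From Sample size calculation: difference 8, SD 20 (standardised difference 8/20 = 0.40), alpha 0.05, power 0.80, 131 per group, 20% dropout, 314 in total. Assumed here because the article does not state them: a two-sided test and the same dropout in both arms. The arm splits below are illustrative.

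**1. Reproducing 314.** 2 × 131 = 262, and 262 × 1.20 = 314.4, which gives 314. The allowance was multiplied on.

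**2. Total that would protect 131 per group.** 262/(1 − 0.20) = 327.5, so 328 (131/0.80 = 163.75, so 164 per group). That is 14 more than 314, provided the arms are equal.

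**3. What 314 delivers.** 314 × 0.80 = 251.2, so about 251 evaluable, or 125 to 126 per group if equal. The shortfall against 262 is 11 in total, 5 to 6 per group. The loss that 314 can absorb while keeping 262 is 1 − 262/314 = 16.6%.

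**4. Reproducing 131.** Normal approximation: n per group = 2 × SD² × (z for alpha + z for power)²/difference².

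- 80% power, two-sided 0.05: 2 × 400 × (1.960 + 0.842)²/64 = 98.1, so 99. The exact t calculation gives 99.1, so 99 to 100.
- 90% power, two-sided 0.05: 2 × 400 × (1.960 + 1.282)²/64 = 131.3. The exact t calculation gives 132.3.
- 80% power, one-sided 0.05: 77.3, so 78.

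The figure of 131 does not follow from the stated 80% power on either reading of sidedness. It matches 90% power, two-sided. The exact t-test power with 131 per group is 89.7%.

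**5. Cost of the dropout slip alone.** With equal arms, power is 89.7% at 262 evaluable and 88.4% at 251, a loss of about 1 percentage point. Both are above 80%.

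**6. Effect of an uneven split.** Two-sided t test, unadjusted, 251 evaluable in total:

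| Split | Evaluable in smaller arm (about) | Power |
|---|---|---|
| 50:50 | 125 | 88.4% |
| 60:40 | 100 | 87.1% |
| 70:30 | 75 | 82.5% |
| 73:27 | 68 | 80.0% |
| 75:25 | 63 | 78.0% |
| 80:20 | 50 | 71.4% |

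Power crosses 80% at about 73:27. Even with no dropout, 314 recruits put at least 131 in each arm only if the smaller arm takes at least 131/314 = 41.7%, so the larger no more than about 58%.

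**The case against.** The strongest reply is that 131 is the wrong yardstick. On the article's own difference, SD, alpha and power, about 99 per group would do: 99/0.80 = 123.75, so 124 per group and 248 in total. The planned 314 exceeds that, and 251 evaluable exceeds the roughly 198 to 200 needed. This stands, and it limits the consequence. It does not make the dropout sentence right, because the article itself calls 131 per group required and its own dropout rate does not deliver that number.

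A reader might go further and infer that the trial is underpowered, or that preference allocation puts its power at serious risk. The documents do not support that. The dropout slip costs about 1 point of power. An uneven split is a separate matter and only a scenario, since the article reports no expected or observed split. Even 80:20 leaves about 71%, which is below target but far from a total loss.

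It can also be said that targets per arm may stand in a fuller protocol that is not shown. That is fair, so the absence of a quota is not raised as a fault. The split matters here only for saying what 314 recruits can be expected to achieve. The disagreement between 131, 20% and 314 is printed in the article and does not depend on anything unseen.

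**Conclusion.** The sample size section is wrong as written, in two linked ways. First, 314 does not protect 131 per group against 20% dropout: it leaves about 251 evaluable, 11 short of 262, and covers only a 16.6% loss. Second, 131 per group does not belong with 80% power. It gives about 90%, while 80% needs about 99 to 100.

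The second error cushions the first. With 251 evaluable and equal arms, unadjusted power is about 88%, and it stays at or above the stated 80% up to a split of about 73:27. The stated power is therefore not threatened by the dropout slip alone. It would be missed only under a markedly uneven split, which the article neither predicts nor reports.

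The dropout arithmetic needs no assumption beyond the printed figures. The power figures rest on a two-sided 0.05 test, equal dropout in both arms, the assumed difference and SD, and an unadjusted comparison. Any adjustment for self-selection is not counted. This is a definite error of modest consequence that should be corrected.

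**What to change.** Recruitment can stay at 314. Reword the sample size section so that it:

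- states that, with 20% loss, about 251 participants are expected to be evaluable (125 to 126 per group if the arms are equal);
- reconciles the per-group number with the power, either 131 with about 90% or about 99 to 100 with 80%;
- states whether alpha is one- or two-sided;
- notes that 328 recruits in equal arms would be needed to keep 131 per group after 20% loss;
- gives the unadjusted power for splits from 50:50 to 80:20, as tabulated above, with the assumption of equal dropout made plain.

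The cost is a few sentences and a short table. The only downside is that the stated evaluable number becomes slightly less favourable.

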### Statistical analysis

All statistical analyses will be performed using SPSS 25.0 (IBM Corporation, Armonk, NY). Continuous variables are described as means and standard deviation. We will use independent *t* tests or Mann-Whitney *U* tests to compare 2 groups. If needed, the stratified analysis will be conducted based on the age of participants and the PRP injection site. A *P* value < .05 will be defined as statistically significant.

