### Outcome measures

#### Primary outcomes

The primary outcomes of our study are the Constant-Murley score (CMS) and visual analog scale (VAS). The shoulder function of the patients will be measured by adopting CMS. CMS is a self and examiner based tool, including pain, the activity of daily life, range of motion, and muscle strength [26]. The total score is 100 and divide into four levels, excellent (< 11), good (11–20), fair (21–30), and poor (> 30) [27]. The overall shoulder pain will be assessed through a VAS, with a score of 0 (no pain) to 10 (maximal pain).

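### Patients choose their own arm, yet the only unconditional comparison is an unadjusted t or Mann-Whitney test, so measured baseline differences between choosers and non-choosers pass into the primary result

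*Protocol article*

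**What the plan says.** The abstract describes allocation by preference: "Participants were assigned to the experiment group (PRP plus physiotherapy) or control group (PRP) by their desire". The section on study setting and participants agrees: "The participants voluntarily choose to receive rehabilitation programs after PRP injection, then PRP in addition to physiotherapy group and PRP group were formed". The aim at the end of the Background, and the hypothesis in the Discussion, are comparative: PRP with early physiotherapy is expected to do better than PRP alone.

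For that comparison the Statistical analysis section gives one sentence on method: "We will use independent *t* tests or Mann-Whitney *U* tests to compare 2 groups". The next sentence adds: "If needed, the stratified analysis will be conducted based on the age of participants and the PRP injection site". The article names no regression, baseline adjustment, matching or weighting.

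The primary outcomes are the Constant-Murley score (CMS) and the pain VAS. Table 1 shows that CMS, VAS, SF-12 and MRI tear size are all recorded at baseline.

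In its limitations the Discussion concedes that the design is not randomized and that the evidence level is lower for it. It continues: "we select non-randomized study with a large sample size to clarify the correlation between PRP and physiotherapy".

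**The concern.** When patients pick their own arm, those who want physiotherapy may differ from those who do not in shoulder function, pain, quality of life, tear size, age or motivation. A two-sample test attributes the whole difference in means to group. It cannot separate an effect of physiotherapy from the prognosis of the people who asked for it.

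The conditional stratification does not close the gap. Nothing says what would make it necessary, so the decision could be taken after the results are seen. It also leaves out the baseline scores and tear size, although these are collected and are obvious candidates for prognostic factors.

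A larger sample narrows the standard error around whatever the test estimates. If that quantity contains a selection difference, a larger sample makes the difference more likely to reach significance. What is at stake is the trial's central conclusion on whether added physiotherapy helps.

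**Working it through.** **Inputs from the protocol article (Sample size calculation).** The article states "we consider that the change of Constant score could be 8 with a standard deviation of 20" and "We calculate that 131 participates for each group will be required with alpha set at 0.05 and a power of 0.8". I read 8 points as the between-group difference and assume a two-sided test, since the article does not give the sidedness. 

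**Inputs that are assumed.** The documents give no baseline imbalance, no correlation between baseline and follow-up, and no expected split between the arms. I take equal arms of 131 and show a range for the rest.

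**1. The plan's own figure.** n per group = 2 × 20² × (1.960 + 0.842)² / 8² = 98.1, so 99 at 80% power. The stated 131 does not follow from 80% power. With SE = 2.471 (step 2), 131 per group gives power Φ(8/2.471 − 1.960) = Φ(1.277) = 0.90. That is a separate matter. Here 131 is used only as the number the plan expects to analyse per arm.

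**2. Standard error.** SE = 20 × √(2/131) = 2.471 CMS points.

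**3. False-positive rate under selection bias.** Suppose physiotherapy has no effect but selection shifts the mean difference by b points. The chance that the 5% test rejects is P(|Z + b/SE| > 1.96):

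| Assumed net bias b (CMS points) | b/SE | Chance of p < 0.05 |
|---|---|---|
| 0 | 0 | 5.0% |
| 1.5 | 0.61 | 9.3% |
| 2.5 | 1.01 | 17.3% |
| 4 | 1.62 | 36.7% |
| 5 | 2.02 | 52.5% |

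**4. A larger sample does not help.** At 157 per arm (half of 314) SE = 20 × √(2/157) = 2.257. For b = 3 the rate goes from 22.9% at 131 per arm to 26.5%. For b = 5 it goes from 52.5% to 60.1%.

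**5. Size and direction from a baseline imbalance.** Let the arms differ at baseline by d points, with baseline–outcome correlation ρ and equal SDs at both times. The bias is ρ × d if the follow-up score is tested, and (ρ − 1) × d if the change score is tested. For d = 5 and ρ = 0.5:
- follow-up score: 0.5 × 5 = +2.5 points
- change score: (0.5 − 1) × 5 = −2.5 points

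Either is 2.5/8 = 31% of the target difference, with opposite signs. Over d = 2 to 10 points (0.1 to 0.5 SD) and ρ = 0.3 to 0.7, the bias on either scale runs from 0.6 points (0.3 × 2) to 7 points (0.7 × 10). The Statistical analysis section does not say which scale is tested, while the sample size section speaks of change.

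**6. Room for an adjusted analysis.** n per group at 80% power ≈ 98.1 × (1 − ρ²)/(1 − R²), where ρ is the covariate–outcome correlation and R² the share of treatment choice explained by the covariates. For ρ from 0 to 0.7 and R² from 0 to 0.3 (both assumed) this gives 51 to 141. At ρ = 0.5 and R² = 0.3 it is 106. Of the values tried, only ρ = 0 with R² = 0.3 (141) exceeds 131.

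**The case against.** **The detail may sit in an unseen analysis plan.** The article is condensed, and covariate lists, propensity models and balance checks are commonly left to such a plan. That stands: the absence of a covariate list is no fault in itself. The article does not defer the comparison, however. It names the test, and that test is unsuitable for self-selected groups.

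**The unadjusted test might be read as the only analysis planned.** It is not, because a stratified analysis by age and injection site is mentioned. What holds is that the unadjusted test is the only comparison planned without a condition.

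**The limitation is disclosed.** The Discussion concedes the design, rates the evidence lower and speaks of correlation. A reader might infer that the large sample is offered as a cure for confounding, but the text does not say so outright. Even so, disclosure does not alter the primary test, and the aim and hypothesis remain comparative.

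**The size is assumed.** This stands. A reader might infer that the result is known to be biased, or biased towards physiotherapy. The documents support neither: no imbalance has been reported, and the sign reverses between follow-up and change scores. Equal arms are not assured either. With a 2:1 split of 262 (175 and 87), SE = 20 × √(1/175 + 1/87) = 2.62, and the four rates fall to 9%, 16%, 33% and 48%. That is lower, but of the same order.

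**Adjustment guarantees nothing.** Correct. No analysis of this design controls type I error against unmeasured factors such as motivation. Adjustment removes only the part carried by measured covariates.

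**Conclusion.** The point holds and should be settled before the groups are compared. The article pairs preference-formed arms with an unadjusted primary test, and neither the conditional stratification nor the acknowledged limitation repairs this.

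The size is conditional. With equal arms of 131, SD 20 and a two-sided 5% test, assumed net biases of 1.5 to 5 CMS points raise the false-positive rate from 5% to between 9% and 53%. The structural weakness does not depend on any one of these values. The documents do not establish that a bias of a given size or direction is present, or that an adjusted analysis would yield a causal effect.

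**What to change.** Replace the sentence naming the t and Mann-Whitney tests, so that:

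- The primary comparison is a regression of the outcome on group (ANCOVA or a mixed model), adjusted for prespecified covariates that are already collected and measured before physiotherapy starts: baseline CMS, VAS and SF-12, MRI tear size, age and injection site. The outcome scale is stated.
- The unadjusted test is kept as descriptive only, and the conditional wording on age and injection site is deleted.
- Two sensitivity analyses are added: a propensity-weighted comparison with standardised baseline differences, and an assessment of unmeasured confounding, for example an E-value.
- The conclusion is worded as an adjusted association.

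The baseline timing must be reconciled first. The Study design section puts the first visit two days before the PRP injection, whereas Table 1 and the Data management section put the baseline assessment two days after it. The Physiotherapy protocol starts physiotherapy two days after the injection. As it stands, a baseline score cannot be shown to precede physiotherapy.

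The cost is new analysis wording and some programming, with no new data or patients. Under most of the assumptions tried, 131 per arm is enough. The remaining drawback is that unmeasured confounding can be assessed but not removed.

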#### Secondary outcomes

Tear size change assessed by MRI, the quality of life evaluated by Medical Outcomes Study Short Form 12-Item (SF-12), and adverse events will be recorded as secondary outcomes. An independent radiologist will assess tear size through MRI before PRP injection and 12 months follow-up. The SF-12 is a 12-item questionnaire, focusing on physical functioning, social functioning, bodily pain, vitality, role physical, role emotional, general health, and mental health [28]. In addition, any adverse events caused by PRP injection and physiotherapy will be recorded via self-report. The outcome indicators will be assessed at five different times by a blinded physiotherapist (Table 1).

**Table 1 Tab1:** Schedules for follow-up assessments and data collection

Assessments	Baseline (Two days after PRP injection)	Finish manual therapy			
		1 month	3 months	6 months	12 months
CMS	√	√	√	√	√
VAS	√	√	√	√	√
SF-12	√				√
Adverse effects	√	√	√	√	√
Tear size	√				√

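### For CMS and VAS, measured five times in self-selected groups, the plan names only unadjusted two-sample tests; a baseline-adjusted repeated-measures model would use the data better

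*Protocol article*

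**What the plan says.** The Protocol article lists CMS and VAS as primary outcomes. Under Secondary outcomes it states: "The outcome indicators will be assessed at five different times by a blinded physiotherapist". Table 1 marks CMS and VAS at all five times: baseline and 1, 3, 6 and 12 months.

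The analysis of these outcomes is given in two sentences of the Statistical analysis section. The first compares the groups by "independent *t* tests or Mann-Whitney *U* tests"; the second reads: "If needed, the stratified analysis will be conducted based on the age of participants and the PRP injection site". No regression or repeated-measures model is named. The section does not name the visit tested, or say whether the score or its change is compared.

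The Sample size calculation section gives the planning values, "we consider that the change of Constant score could be 8 with a standard deviation of 20", and the allowance for loss, "Considering the 20% drop rate, we will recruit 314 participates in total". The Study setting and participants section says that the groups form by the patients' own choice.

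**The concern.** A t test or a Mann-Whitney test takes one number per patient. Three things follow from naming only these tests.

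- **Baseline.** Neither test adjusts for the baseline score by regression. Groups formed by choice may differ at baseline, and a test on raw follow-up scores carries part of that difference into the estimated effect.
- **Intermediate visits.** Scores at 1, 3 and 6 months cannot inform the 12-month comparison. They are the best available information on patients who later leave.
- **Loss.** Without imputation the test uses only patients with a value at the tested visit. If loss depends on earlier scores and differs between the groups in rate or in kind, that comparison can be biased.

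At stake are precision that the collected data could supply, and some protection against baseline imbalance and selective loss in a design that lacks randomisation.

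**Working it through.** **Inputs from the article.** CMS difference 8, SD 20, alpha 0.05 (taken as two-sided), power 0.80, 131 per group, 20% loss, 314 recruited. The correlation r between baseline and follow-up CMS is not given; 0.3 to 0.7 is assumed.

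**The plan's own figure.** n per arm = 2 × (1.960 + 0.842)² × 20² / 8² = 98.1, so 99. The stated 131 does not follow from the stated inputs. It is close to the 132 needed for 90% power (power at 131 is 89.9%). The total 314 is 262 × 1.2 = 314.4, whereas 262 / 0.8 gives 328. That is a separate matter; 314 is taken as given here.

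**Unadjusted test after loss.** 314 × 0.80 = 251, about 125 per arm if choice splits evenly. SE = 20 × √(2/125) = 2.53. Power = Φ(8/2.53 − 1.96) = Φ(1.20) = 88.5%.

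**Baseline-adjusted comparison.** If SD 20 is the SD of a score at one visit, adjustment multiplies the variance by 1 − r². If it is the SD of change, adjustment multiplies the variance of the change-score test by (1 + r)/2.

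| r | Factor, single-visit SD | SE | Power | Factor, SD of change | SE | Power |
|---|---|---|---|---|---|---|
| 0.3 | 0.91 | 2.41 | 91.2% | 0.65 | 2.04 | 97.5% |
| 0.5 | 0.75 | 2.19 | 95.5% | 0.75 | 2.19 | 95.5% |
| 0.7 | 0.51 | 1.81 | 99.3% | 0.85 | 2.33 | 92.9% |

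**Baseline difference.** With equal SDs and a within-group slope of r, each point of baseline difference between the groups puts r points (0.3 to 0.7) into a raw-score comparison. It puts r − 1 points (−0.7 to −0.3) into a change-score comparison.

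**Attrition, illustration only.** The document gives no loss by group or by score. Suppose there is no true effect, SD is 20, all visits are equally correlated at r, and the chance of loss after 6 months is Φ(a − 0.8 z), where z is the standardised 6-month score. The mean 12-month score of those who stay is then shifted by 20 × r × (0.8/√1.64) × φ(c)/Φ(c), where Φ(c) is the proportion kept.

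- At 28% loss (a = −0.75, c = 0.586): 20 × 0.625 × 0.466 × r = 5.82r, or 1.7, 2.9 and 4.1 points at r = 0.3, 0.5 and 0.7.
- At 15% loss (c = 1.036): 20 × 0.625 × 0.274 × r = 3.43r, or 1.7 points at r = 0.5.

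The bias in the raw 12-month difference among completers is therefore:

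- same rate and mechanism in both groups: zero;
- same mechanism, 28% v 15%: 2.9 − 1.7 = 1.2 points at r = 0.5;
- score-dependent 28% loss in controls only, random 15% loss in the other group: 1.7 to 4.1 points.

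In the last two cases the sign is against physiotherapy. In the last case, adjusting completers for baseline alone leaves about 5.82 × (r − r²) = 1.2 to 1.5 points; a model that also uses the 6-month score removes the bias. That success is built into the illustration, because loss was made to depend only on an observed score.

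For a change score, the bias in that case is 5.82 times the gap between the 6-to-12-month and the 6-month-to-baseline correlations. It is zero if these are equal and about 1.7 points if the gap is 0.3.

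**The case against.** The strongest reply is that several harsher readings go beyond the text. It is largely right about them.

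- A reader might infer that baseline is ignored. The Sample size calculation section speaks of a change in the Constant score, so the tests may be run on change from baseline, which does use it. What stands is that baseline is not adjusted for by regression, and that the Statistical analysis section never says change is compared.
- A reader might infer that one visit is tested and absent patients are dropped. The article states no tested visit and no missing-data rule. The latter is commonly left to an analysis plan, which is not shown, so its absence is no fault. What the named tests can use, absent imputation, is a property of the tests.
- A reader might infer that controls have no therapist contact and so will leave more often. The Study design section has participants visit a physical therapist before injection and at 1, 3, 6 and 12 months, without limiting this to one group. Controls lack the treatment sessions only. Unequal loss is possible but not shown.
- A reader might take a bias of about 3 points as the expected size. That is one asymmetric scenario at r = 0.5; with the same mechanism in both groups it falls to about 1 point or to zero.
- A reader might conclude that the trial is underpowered. On its own inputs the simple test has 88.5% power after loss.

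Leaving the choice between the t and the Mann-Whitney test open is ordinary shorthand in an article and adds little weight.

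The core survives. The article commits to a method, and that method suits five repeated measurements in self-selected groups poorly. This is a better method in place of a stated one, not a request for missing detail.

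**Conclusion.** The point holds as a recommended improvement. The gain in power is from about 88% to 91-99% (single-visit SD) or 93-97% (SD of change), with about 125 per arm, an even split and an assumed r of 0.3 to 0.7. The planned test already exceeds its 80% target, so the trial does not depend on this change for power.

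The effect on bias cannot be sized from the document. The illustrations run from zero to about 4 points against a target of 8, and a mixed model removes such bias only if loss is missing at random given the observed data. Adjustment deals with measured baseline differences; it does not remove unmeasured confounding from patients choosing their own group.

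**What to change.** First reconcile when baseline is taken. The Study design section places it two days before injection; Table 1 and the Data management section place it two days after. A score cannot serve as the baseline covariate until this is settled.

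Then replace the sentence on two-group tests with, for each primary outcome:

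- one mixed model for repeated measures over 1, 3, 6 and 12 months (SPSS MIXED, in the software already named);
- terms for group, visit, group-by-visit, baseline score and baseline-by-visit;
- pre-specified baseline confounders listed in the text, including age and injection site, which the plan already names for stratification;
- the 12-month group contrast with its 95% confidence interval as the reported result;
- the rank test kept as a sensitivity analysis.

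The cost is a change of wording and modest programming, with no new data. The downside is reliance on missing at random, which should be stated alongside the result.
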